### Secondary outcomes

% Difference in 7-point Likert scale and GRSC (Table 2):T0 and all other time points specified aboveTime to discharge from the endoscopy unit% Change in cumulative narcotic use for the previous 3-day period:T0 vs T60 daysT0 vs T120 daysRate of all intervention-specific adverse events (Using the American Society of Gastrointestinal Endoscopy classification) [10]Survival

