### Study population

All patients referred for EUS for suspected pancreatic malignancy or for neurolysis for pain due to proven pancreatic malignancy are eligible. The study will be presented to them by a single research assistant, who will also obtain study consent before the procedure. Patients will be randomized if they meet all inclusion criteria and have no exclusion criteria presented in Table 1.

**Table 1 Tab1:** Inclusion and exclusion criteria for the study

**Inclusion criteria**	1. Malignant-appearing pancreatic mass, or proven pancreatic cancer involving the pancreatic genu, body, or tail on imaging done before the endosonography 2. Any level of abdominal or back pain considered to be potentially related to the mass: a. New onset pain (< 3 months) b. Constant c. Centrally located d. With or without irradiation to the back e. No obvious other source of pain 3. No possibility of immediate surgical management. (Based on EUS evidence of venous involvement ≤ 1 cm from portal confluence and/or arterial involvement of the celiac axis or the splenic artery ≤ 1 cm from the bifurcation of the celiac axis, and/or evidence of liver metastases) 4. Signed, informed consent 5. Celiac axis accessible for *bilateral* neurolysis at EUS
**Exclusion criteria**	1. Allergy to bupivacaine 2. Tumors amenable for curative resection 3. Significant coagulopathy (platelets < 50000 µ/L, INR > 1.4, uninterrupted use of oral anticoagulants at therapeutic dosage [except for antiplatelet agents] 4. Patients with concurrent sepsis 5. Previous EUS CPN

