**Fig. 1 Fig1:**
[figure not shown]
Schedule of enrolment interventions and assessments

Immediate post-procedural surveillance:Likert pain scores pre-procedure (T0) and 30 min after arriving in recovery (T30) and then every 30 min until dischargeOpioid use in the last 3 days before the procedureVital signs pre-procedure (T0), immediately before and after neurolysis, and at 30 min after arriving in recovery (T30), and then every 30 min until dischargeRequirements for analgesia during the recovery period

Post-discharge surveillance:

Telephone interviews by a single research assistant on days 3, 7, 30, 60, 90, and 120* for:7-point Likert scale for pain (Table 2)Global rating scale of change (GRSC) (Table 2)Any adverse events (diarrhea, fever, dizziness, leg weakness)Hospital visitsNarcotic use.

**Table 2 Tab2:** Likert pain scale and GRSC

**7-point Likert scale for pain**	0 No discomfort at all 1 Minor discomfort 2 Mild discomfort 3 Moderate discomfort 4 Moderately severe discomfort 5 Severe discomfort 6 Very severe discomfort
**Global rating scale of change (GRSC)**	0 No improvement at all 1 Minor improvement 2 Mild improvement 3 Moderate amount of improvement 4 Quite a bit of improvement 5 A lot of improvement 6 Great improvement

*Days 3 and 7: ± 2 days; days 30, 60, 90, and 120: ± 4 days

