## Outcomes

### Primary outcome

Comparative change in Likert pain scores before procedure (T0) and at 30 days after the procedure (Table 2) with treatment failure defined as less than 3-point decrease in Likert pain scores.

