### Statistical analysis

Descriptive statistics will assess patient characteristics (demographics, tumor size) and the balancing of randomization. The data will be tested for normality, and the paired Wilcoxon ranked sum test will assess the pain scores. Student’s *t* test will be performed when comparing two means. Fisher’s exact method will be used for proportions comparison. All *p*-values are two-tailed, and values < 0.05 will be considered statistically significant. Subsequent logistic regression modeling will determine the factors that are associated with a better pain outcome.

Kaplan-Meier estimates of the survival curve will be obtained for each treatment group, and statistical comparisons of these will be performed using the log-rank test. The Cox proportional hazards models will be used to study survival while adjusting for potential confounding factors.

Patients who withdraw will be noted and will be noted and they will be excluded from analysis.

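### The secondary pain outcome is a percentage of T0 on a 0–6 ordinal score, which gives low-baseline patients disproportionate weight; the score adjusted for T0 would serve better at no cost

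*Protocol article*

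**What the plan says.** All references are to the protocol article.

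- **Secondary outcomes** lists a percentage "Difference in 7-point Likert scale" (and, in the same line, GRSC), comparing T0 with all the other scheduled times.
- **Table 2** defines the pain score by ordered labels, from "0 No discomfort at all 1 Minor discomfort 2 Mild discomfort 3 Moderate discomfort" up to "6 Very severe discomfort".
- **Table 1, inclusion criterion 2** admits "Any level of abdominal or back pain considered to be potentially related to the mass". No minimum score is set.
- **Primary outcome** works in points: "Comparative change in Likert pain scores before procedure (T0) and at 30 days after the procedure", with "treatment failure defined as less than 3-point decrease in Likert pain scores".
- **Statistical analysis** states that "the paired Wilcoxon ranked sum test will assess the pain scores" and that Student's t test is used to compare two means. It ties neither test to the percentage outcome.

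The article does not say whether the percentage is taken per patient or from arm means, or whether it is summarised by a mean or a median.

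**The concern.** Dividing by T0 makes the value of one pain category depend on where the patient started. With no floor on baseline pain, patients at T0 = 1 or 2 can enter, and for them a small shift is a very large percentage. The scale is also lopsided: relief cannot exceed −100%, but worsening can go far beyond +100%.

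This outcome carries all pain results except the day-30 primary comparison, including recovery-room pain (a stated secondary aim) and durability to day 120. Two things are at stake: a summary that may disagree in direction with the primary outcome's scale, and precision lost by not using T0 as a covariate although it is already collected.

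**Working it through.** The article gives no figure for this outcome, so there is none to reproduce.

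**Inputs from the article:** score 0–6 (Table 2); any pain level at entry (Table 1); 90 per group (Sample size calculations).

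**Step 1, the percentage scale.** Per-patient percentage = 100 × (follow-up − T0) / T0. One category is worth 100 / T0, and the largest possible worsening is 100 × (6 − T0) / T0.

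| T0 | one category | largest improvement | largest worsening |
|---|---|---|---|
| 1 | 100% | −100% | +500% |
| 2 | 50% | −100% | +200% |
| 3 | 33.3% | −100% | +100% |
| 4 | 25% | −100% | +50% |
| 5 | 20% | −100% | +20% |
| 6 | 16.7% | −100% | 0% |

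**Step 2, direction can reverse (constructed data).** In Arm A, 81 patients go from 5 to 2 and 9 go from 1 to 4. In Arm B, 81 go from 5 to 3 and 9 stay at 1.

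- Points, A: (81 × −3 + 9 × 3) / 90 = −2.40. Points, B: (81 × −2 + 9 × 0) / 90 = −1.80. A is better.
- Mean percentage, A: (81 × −60 + 9 × 300) / 90 = −24.0%. Mean percentage, B: (81 × −40 + 9 × 0) / 90 = −36.0%. B is better.
- Median percentage: −60% against −40%. A is better.
- Percentage of arm means: the baseline mean is (81 × 5 + 9 × 1) / 90 = 4.60, so −2.40 / 4.60 = −52.2% against −1.80 / 4.60 = −39.1%. A is better.

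The reversal therefore needs the mean of per-patient percentages; the other two summaries do not show it here.

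**Step 3, how much weight low baselines carry (assumed change SD 1.5, mean change −1 or −2 points).** With 5% of patients at T0 = 1, those patients supply 13–22% of the variance of the percentage, against 3–4% of the variance of the change in points. With 2% at T0 = 1 the share is 7–12%. With T0 spread evenly over 1–6 (17% at T0 = 1) it is 33–49%.

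**Step 4, power (simulation).** Assumptions: 90 per arm; true difference 0.75 point; residual SD 1.5; mean follow-up score 2; follow-up rising 0.3 to 0.8 point per baseline point; scores rounded and clipped to 0–6; T0 ranging from even over 1–6 to mostly 4–6.

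| Analysis | Power |
|---|---|
| t test on percentage | about 70–84% |
| rank test on percentage | about 81–86% |
| t test on unadjusted change in points | about 63–83% |
| score adjusted for T0 (linear model) | about 87–88% |

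Repeat runs move these by a point or two. Type I error stays near 5%.

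**Step 5, how often the directions disagree (same model, mean percentage against mean points).** Opposite signs occur in 17–21% of trials with no true difference, and in 1% or less with a 0.75-point effect. A separate model with a 0.5-point effect gave 2–4%.

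**The case against.** The strongest reply is that the article never specifies a per-patient percentage, an arithmetic mean or a t test. A median or a percentage of arm means would be less affected, and the choice may sit in an analysis plan that is not shown. The test named for pain scores is rank-based, and a rank test on the percentage recovers much of the lost power, in some scenarios nearly all of it. The power loss also cannot be charged to the percentage itself, since unadjusted change in points does no better. Sign conflict at zero effect is a comparison of two noise estimates.

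Most of this stands and limits the claim. Two parts do not settle it. The named Wilcoxon test is described as paired, which compares times within patients and not independent arms, so the article does not secure a rank comparison between arms. And an analysis plan can choose how to summarise the percentage, but the outcome the article names is still a percentage of ordered labels.

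A reader might infer that a few low-baseline patients dominate this outcome, or that its between-arm result depends mainly on them. The documents do not support that. They give no baseline distribution, and under moderate-to-severe baselines the influence is disproportionate without being dominant. A reader might also infer that the outcome is likely to contradict a real effect; the simulation shows this is rare.

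**Conclusion.** The point holds in limited form. A percentage of T0 on a 0–6 ordinal score, with no minimum pain at entry, is a poor choice of secondary outcome. If averaged per patient, it over-weights low baselines and can disagree in direction with the primary outcome's scale, chiefly when the arms truly differ little. That case matters here because the investigators expect no influence of bupivacaine on intra- or immediate post-procedural pain (Objectives and design).

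Under the stated assumptions, adjusting for T0 raises power to 87–88%, from 70–84% (t test on the percentage) or 81–86% (rank test on it). The gain is due to the adjustment and not to points as such. The size depends on an assumed effect, residual SD, baseline mix and baseline-to-follow-up slope, none of which the article gives. Validity is not threatened, and the primary outcome is unaffected. This is a free improvement to a secondary outcome.

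**What to change.** In Secondary outcomes, replace the percentage for the Likert score with the between-arm difference in Likert score at each scheduled time point, adjusted for the T0 score by linear or ordinal regression with T0 as covariate. Name the same model in Statistical analysis. Keep percentages as description only, and say how they are formed. Changing to unadjusted change in points would not be enough, because it brings no clear gain in power.

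The cost is a line of wording in each place and the notification to the ethics board that the article already foresees for protocol changes. No new data or patients are needed, since T0 and all follow-up scores are already collected. The change should be made before the data are analysed.

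### Narcotic use has no listed comparison at day 30, the primary pain time point; its percent-change form can fail at zero or low baselines, and a percent difference from T0 cannot be computed for the GRSC

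*Protocol article*

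**What the plan says.** All references are to the protocol article.

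- **Primary outcome:** "Comparative change in Likert pain scores before procedure (T0) and at 30 days after the procedure", with treatment failure defined by the size of the fall in score.
- **Patient follow-up, post-discharge surveillance:** "Telephone interviews by a single research assistant on days 3, 7, 30, 60, 90, and 120". The items asked at these calls are the Likert pain score, the GRSC, adverse events, hospital visits and narcotic use.
- **Patient follow-up, immediate surveillance:** the pre-procedure items include opioid use over the preceding 3 days and "Likert pain scores pre-procedure (T0) and 30 min after arriving in recovery (T30"). The GRSC is not among them.
- **Secondary outcomes, narcotics:** percent "Change in cumulative narcotic use for the previous 3-day period:T0 vs T60 daysT0 vs T120" days. Day 30 is not listed.
- **Secondary outcomes, scales:** percent "Difference in 7-point Likert scale and GRSC (Table 2):T0 and all other time points". One heading covers both scales.
- **Table 1:** the pain criterion is "Any level of abdominal or back pain considered to be potentially related to the mass". No criterion concerns opioid use.
- **Table 2:** the GRSC begins "0 No improvement at all 1 Minor improvement 2 Mild improvement 3 Moderate amount of improvement" and ends at great improvement (score 6).

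**The concern.** Pain at day 30 is scored under whatever opioids the patient is then taking. If neurolysis works less well in one arm and those patients take more opioid, the Likert scores of the two arms can look alike. The Objectives and design section calls the trial non-inferiority, so similar pain scores may well be the result to be interpreted. The opioid comparison that would help a reader judge it is not listed for that day. Days 60 and 120 do not fully replace it: follow-up ends at death, so the later comparisons cover survivors only.

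The other two issues concern how outcomes are expressed. A percent change needs a baseline that is not zero and not very small, and eligibility guarantees neither for opioid use. The GRSC has no baseline score at all, so a percent difference from T0 does not fit it.

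At stake are the clarity of one supportive comparison for the primary result and two secondary outcomes that the protocol itself chose to specify.

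**Working it through.** The plan states no figure for this point to reproduce. The only design figure used is 90 per group, from the Sample size calculations section, and it serves only as a denominator.

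**Step 1. Assessment schedule against outcome list**

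| Call (day) | Narcotic use asked | Narcotic comparison with T0 listed | Likert comparison with T0 listed |
|---|---|---|---|
| 3 | yes | no | yes |
| 7 | yes | no | yes |
| 30 | yes | **no** | yes (primary) |
| 60 | yes | yes | yes |
| 90 | yes | no | yes |
| 120 | yes | yes | yes |

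At day 30 the pain comparison has no opioid comparison beside it, although narcotic use is asked about at that call.

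**Step 2. Percent change per patient**

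Percent change = 100 × (F − B) / B, where B is 3-day use at T0 and F is 3-day use at follow-up. The values below are illustrative and not from the protocol.

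| B | F | Percent change | Absolute change |
|---|---|---|---|
| 0 | 0 | 0/0, undefined | 0 |
| 0 | 30 | 30/0, undefined | +30 |
| 5 | 30 | 100 × 25/5 = +500% | +25 |
| 60 | 30 | 100 × (−30)/60 = −50% | −30 |

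For the last two patients together:

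- The mean of the individual percentages is (500 − 50)/2 = +225%.
- Their total use falls from 65 to 60, which is 100 × (−5)/65 = −7.7%.

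The patient with the low baseline sets the sign of the mean. In the same way, a rise of 20 mg is 20/10 = +200% from 10 mg but 20/300 = +6.7% from 300 mg.

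**Step 3. How many patients could be affected**

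The protocol does not give the share using no opioid at T0. Under assumed shares:

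- 10%: 0.10 × 90 = 9 per arm (18 of 180)
- 20%: 0.20 × 90 = 18 per arm (36 of 180)
- 30%: 0.30 × 90 = 27 per arm (54 of 180)

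**Step 4. The GRSC**

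The formula would be 100 × (G at follow-up − G at T0) / G at T0.

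- The listed pre-procedure items include no GRSC.
- The scale rates improvement, so before the procedure there is nothing to rate.
- If a baseline of 0 (no improvement) were assigned to everyone, the denominator would be 0.

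On either route the quantity has no value for any patient. The schedule figure is not available in the text. A T0 entry for the GRSC there would conflict with the scale's own anchors.

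**The case against.** **Days 60 and 120 are a legitimate choice.** This stands in part. Nothing in the protocol contradicts it, and narcotic use is a secondary aim with no restriction on time points, so day-30 use could still be reported. But the outcome list is explicit, and it leaves out the day on which the comparison would help most.

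**The primary result is interpretable anyway.** This stands. A reader might infer that day-30 pain cannot be interpreted without same-day opioid use. The documents do not support that: allocation is randomised, the patient and the nurse collecting the data are blinded, and a comparison of pain under the opioids actually taken is meaningful. Opioid use affects what a similarity in pain means, not whether the comparison is valid.

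**Percent change may not be per patient, and zero baselines belong in the analysis plan.** This stands in part. The protocol does not say at which level the percentage is taken. A percent change in an arm's mean or total is defined as long as that baseline mean or total is above zero. A reader might also infer that opioid-free patients are to be dropped, but no such rule appears. An analysis plan not shown here could deal with zeros. The percent form, however, is fixed in the protocol, and a zero rule would not cure the instability of individual percentages at low baselines.

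**The GRSC line is only compressed wording.** It could be meant as a list of assessment times or as a between-arm difference. The wording ties a percent difference to T0 for both scales, so neither reading fits it well. The objection is right that the GRSC scores themselves are usable: only the stated form fails, not the data.

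**Conclusion.** The point holds, in three limited parts.

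1. No day-30 narcotic comparison is listed, although narcotic use is asked about then and day 30 is the primary pain time point. This is a weak choice of time points, not a contradiction.
2. Percent change, if taken per patient, is undefined at zero baseline use and unstable at low use. Table 1 permits such patients. How many there will be is unknown: 9 to 27 per arm rests entirely on an assumed share of 10% to 30% and on 90 patients per arm, and is not an estimate for this trial.
3. The GRSC percent difference from T0 cannot be computed for any patient as written. This follows from the scale's anchors and the listed assessments, with no numerical assumption.

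The defects are in secondary outcomes and do not invalidate the primary comparison. They merit correction because the remedy is a better-defined comparison drawn largely from assessments already scheduled.

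**What to change.** - **Add the day-30 comparison.** List T0 versus day 30 for narcotic use and report it beside the primary result as supportive. Write it as day 30, because the protocol already uses T30 for the half-hour recovery assessment.
- **Replace percent change for narcotic use.** Compare 3-day opioid use between arms at days 30, 60 and 120 by ANCOVA, or rank ANCOVA if the amounts are heavily skewed or often zero, adjusted for the T0 amount. Patients with a zero baseline then contribute like any others.
- **Restate the GRSC outcome.** Compare raw GRSC scores between arms at each follow-up call, with no reference to T0.

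The cost is one more secondary comparison and revised wording in the Secondary outcomes section, submitted to the ethics board as the Trial status section requires for any modification. One check is needed: the post-discharge list says only that narcotic use is asked about, so the sponsor should confirm that each call records the amount over the previous 3 days.

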### Statistical analysis

Descriptive statistics will assess patient characteristics (demographics, tumor size) and the balancing of randomization. The data will be tested for normality, and the paired Wilcoxon ranked sum test will assess the pain scores. Student’s *t* test will be performed when comparing two means. Fisher’s exact method will be used for proportions comparison. All *p*-values are two-tailed, and values < 0.05 will be considered statistically significant. Subsequent logistic regression modeling will determine the factors that are associated with a better pain outcome.

Kaplan-Meier estimates of the survival curve will be obtained for each treatment group, and statistical comparisons of these will be performed using the log-rank test. The Cox proportional hazards models will be used to study survival while adjusting for potential confounding factors.

Patients who withdraw will be noted and will be noted and they will be excluded from analysis.

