## Methods

### Objectives and design

The primary hypothesis for this study is that bupivacaine injection before neurolysis dilutes the neurolytic effect of alcohol and therefore decreases its analgesic effectiveness. We also believe that bupivacaine injection has no influence on intra- or immediate post-procedural pain.

The primary aim of study is to compare the effectiveness of EUS-CPN with and without bupivacaine. Secondary aims include a comparison of intra- and post-procedural pain, narcotic use, adverse events, and survival between the studied groups.

This is a single-center, randomized, double-blinded, parallel groups, non-inferiority clinical trial to be performed at the endoscopy unit of the Centre Hospitalier de l’Université de Montréal (CHUM) in Québec, Canada.

The SPIRIT reporting guidelines have been used in protocol formulation [9].

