### Randomization and blinding

Participants will be randomized in 1:1 fashion, by sealed opaque envelopes, prepared by an independent third party, using a list produced by the web-based randomization service Sealed Envelope™.

Since the final inclusion criteria (accessibility of the celiac axis by EUS) is determined during the procedure, while the patient is sedated, the patient will be blinded to the treatment arm.

The research nurse who collects the data will not be present during the randomization process, nor the procedure, and will therefore also be blinded to the treatment arm.

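### The test assigned to the pain scores is misnamed and, read as paired, cannot compare the two randomised arms; no between-arm test is assigned to the primary outcome

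*Protocol article*

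**What the plan says.** Four parts of the protocol article make the primary question a comparison of independent groups.

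- Objectives and design: "The primary aim of study is to compare the effectiveness of EUS-CPN with and without bupivacaine". The trial is described as a "parallel groups, non-inferiority clinical trial".
- Randomization and blinding: "Participants will be randomized in 1:1 fashion". Individuals are allocated, and no matching across arms is described.
- Sample size calculations: the target is a 3-point difference between the two groups, in a formula for two independent means.
- Primary outcome: "Comparative change in Likert pain scores before procedure (T0) and at 30 days after the procedure", with "treatment failure defined as less than 3-point decrease in Likert pain scores". The outcome therefore has a score form (change) and a yes/no form (failure).

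The Statistical analysis section then assigns one test to the pain scores by name: "The data will be tested for normality, and the paired Wilcoxon ranked sum test will assess the pain scores". The same paragraph says that Student's t "test will be performed when comparing two means" and that Fisher's exact method is for proportions. It ties neither to a particular outcome. The log-rank test and Cox model are given for survival.

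**The concern.** The only test tied to the pain scores carries a name that contradicts itself, and its first word points to the wrong comparison. A paired test needs pairs. In this design the only pairs are a patient's own T0 and day-30 scores, so a paired test shows whether pain changed after neurolysis, not whether bupivacaine made a difference.

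The article's Background calls the effectiveness of neurolysis well established, and under Study arms both groups receive 20 mL of absolute alcohol. Both arms should therefore improve, and a before-after test should be significant in each, whatever bupivacaine does. A paired p-value also gives no between-arm estimate or interval, which a trial labelled non-inferiority needs in any case.

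The second problem is assignment. The primary outcome can be read as a change score or as a failure proportion. Wilcoxon, Student's t and Fisher's exact tests are all listed, and none is fixed as the between-arm primary test. The primary p-value could then be picked from several after the data are seen.

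**Working it through.** **1. The plan's own figure.** Sample size calculations gives 2 × 7.8 × (7/3)² per group. The printed product is 2 × 7.8 × 5.4 = 84.24, or 84.93 with (7/3)² left unrounded, against the stated 90. The standard two-sided formula, 2 × [7 × (1.960 + 0.842)/3]² = 85.5, rounds up to 86. The gap to 90 is a separate matter. What counts here is that this is the formula for two independent groups. A paired calculation with the same inputs would be [7 × (1.960 + 0.842)/3]² = 42.7, about 43 patients, and that is not what the plan used. The trial was sized for a between-arm comparison.

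**2. The two readings of the test name.**

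| Reading | Compares | Answers the primary question? |
|---|---|---|
| Paired (signed-rank) | T0 with day 30, same patient | No |
| Rank-sum on change (unpaired) | Change in one arm with change in the other | Yes, but then the word paired is wrong |

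The sentence cannot stand on either reading.

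**3. What each test detects.** Assumed inputs, not from the article: T0 mean about 4, SD 1.2; day-30 score = T0 minus the arm's fall plus noise of SD 1.5; all scores rounded and kept within 0 to 6; 90 per arm; 1,000 runs; two-sided 5%.

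| True falls (arm 1, arm 2) | Paired test significant, each arm | Rank-sum on change significant |
|---|---|---|
| 2, 2 | 100%, 100% | 4.6% |
| 1, 1 | 100%, 100% | 4.4% |
| 2, 1 | 100%, 100% | 98.4% |

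A separate simulation of a 1-point arm difference (500 runs) gave 97% power for the rank-sum test. The paired result is the same in every row; the unpaired result separates no difference from a real one.

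**4. The other tests in the paragraph, same inputs.** For falls of 2 and 1, Student's t on change had about 99% power and Fisher's exact test on failure about 81%. With equal falls, both rejected in about 5% of runs or fewer. Usable between-arm tests are therefore named; what is missing is their assignment.

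**5. Does correcting the test need more patients?** On the document's inputs, dividing 85.5 by the rank-sum efficiency 3/π gives 85.5 × 3.1416/3 = 89.5, about 90 per group. The stated number would still serve. Whether an SD of 7 suits a 0-to-6 scale is a separate question.

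**6. Gain from adjusting for T0.** With equal variances σ² and correlation r between T0 and day 30, the change score has variance 2σ²(1 − r), and the T0-adjusted comparison has σ²(1 − r²). The ratio is (1 + r)/2. At an assumed r of 0.5 it is 0.75, and at 0.3 it is 0.65, so variance is 25 to 35% lower. The article gives no r.

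**The case against.** The strongest reply is that this is a slip of wording. The term ranked sum suggests that the two-sample test was meant, and valid between-arm tests stand in the same paragraph. Much of that is right, and it limits the point.

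A reader might infer that the trial has no between-arm test for pain, or only the t test. The document does not support this: Fisher's exact test is listed too and fits the failure definition. Nor does it follow that the primary question will go unanswered.

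A reader might also fear a false-positive rate of up to 50% from declaring a difference when only one arm's paired test is significant. If each paired test has power p, that pattern occurs with probability 2p(1 − p), which peaks at 2 × 0.5 × 0.5 = 50%. The peak needs a common fall of only about 0.2 points under the assumed inputs. The rate is about 8% at 0.5 points and 0% at 1 or 2 points. That is at odds with the clear improvement the protocol expects, and the article nowhere says it will compare within-arm p-values.

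Third, leaving T0 out as a covariate is not an error. An unadjusted comparison of change is valid, and such detail is commonly left to an analysis plan. Finally, the article does not say that the normality test selects the primary test; it only places the two side by side.

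What remains is that the article names a specific test for the pain scores and names it wrongly. An analysis plan that followed the sentence would inherit the fault, and one that departed from it would contradict the published protocol.

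**Conclusion.** The point holds in this form: the test assigned to the pain scores is misnamed, its paired reading cannot compare the randomised arms, and no between-arm test is assigned to either form of the primary outcome. The mismatch follows from the text and needs no assumptions.

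The size rests on the simulation inputs, which are assumed. With a clear fall in both arms, the paired test is significant in about 100% of runs regardless of bupivacaine, against about 97 to 98% power and about 5% type I error for the rank-sum test on change. The exact percentages would move with other inputs; the paired test's inability to separate the arms would not. The T0 adjustment is an improvement in precision, not part of the error.

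**What to change.** Reword the Statistical analysis paragraph so that it states the following:

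- **Primary analysis:** a comparison between randomised arms of the T0-to-day-30 Likert change, preferably as the day-30 score adjusted for T0, reported as a between-arm difference with 95% confidence interval.
- **Sensitivity analysis:** the unpaired Wilcoxon rank-sum test on change from T0.
- **Treatment failure:** the proportion in each arm compared by Fisher's exact test.
- **Normality testing:** not used to choose the primary test.
- **Paired signed-rank test:** within-arm description only.

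The confidence interval is also what any non-inferiority conclusion would be read from; this change does not itself settle that criterion. The smallest acceptable correction is to delete the word paired, say that the rank-sum test compares change between arms, and assign Fisher's exact test to failure.

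The cost is one paragraph and a submission to the ethics board, which Trial status already foresees for protocol modifications. T0 and day-30 scores are already collected, so no new data are needed, and the change of test does not call for a larger sample. The article reports 36 patients recruited at the time of writing. The correction should be made before any comparison of outcomes by arm.
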